# Safety planning and transdiagnostic cognitive behavioral therapy for adolescent suicide prevention in Mozambique: study protocol for the SPI/TCBT-S hybrid effectiveness/implementation cluster randomized trial

**DOI:** 10.1186/s12888-025-07102-w

**Published:** 2025-07-01

**Keywords:** Suicide prevention, Safety planning, Cognitive behavioral therapy, Cluster randomized trial, Adolescent health, Mozambique, Hybrid effectiveness/implementation trial

## Abstract

**Background:**

More than 75% of suicide deaths occur in low-and middle-income countries (LMICs) and almost 90% of adolescents who die by suicide live in LMICs. Globally, suicide is the fourth leading cause of death for youth aged 15–29. Six of the top 10 countries by suicide rates in the world are in the African region. Despite this, there are few to no evidence-based youth suicide prevention packages developed for, and tested in, the African context. To address this gap, this study aims to test effectiveness and implementation outcomes for the brief Safety Planning Intervention (SPI) and the more resource-intensive multi-session Transdiagnostic Cognitive Behavioral Therapy Intervention for Suicide Prevention (TCBT-S) delivered by non-specialists in Mozambican secondary schools.

**Methods:**

Using a three-arm, parallel, Hybrid Type-1 cluster randomized trial design, we will randomize 7 secondary schools each to Enhanced Usual Care (EUC), SPI alone, and TBCT-S (21 schools total) to evaluate effects on suicidal behaviors (primary) and suicidal ideation/depressive symptoms (secondary). Exploratory structural equation modeling will examine potential mechanisms of intervention effects. Implementation outcomes, barriers, and facilitators to EUC, SPI, and TCBT-S implementation will be assessed using the RE-AIM evaluation and CFIR determinant frameworks. Costs and cost-effectiveness will be evaluated using a Markov model parameterized with cost and trial outcomes data and be applied to projecting budget impact and potential scale-up to provincial and national levels.

**Discussion:**

This study is innovative in being the first, to our knowledge, to rigorously test SPI and TCBT-S for adolescent suicide prevention in Sub-Saharan Africa. By simultaneously testing the brief SPI alone – as well as integrated into a more resource-intensive TCBT-S – this study will examine whether the potential gains in effectiveness with the more resource intensive TCBT-S justify its scale-up versus the brief SPI intervention. If effective, SPI or TCBT-S have a large potential to be rapidly scaled up to safeguard youth mental health in Mozambique and other similar LMICs.

**Trial registration:**

ClinicalTrials.gov; NCT06465381; https://clinicaltrials.gov/study/NCT06465381.

**Supplementary Information:**

The online version contains supplementary material available at 10.1186/s12888-025-07102-w.

## Background

Youth suicide is a global public health emergency, with the African World Health Organization (WHO) region having the highest suicide rates in the world. More than three quarters of suicide deaths occur in low-and middle-income countries (LMICs) and almost 90% of adolescents who die by suicide live in LMICs [1] Globally, suicide is the fourth leading cause of death for adolescents and young adults aged 15–29 [2] The African WHO region has the highest estimated age-standardized suicide rates in the world, with countries like Mozambique (Fig. 1) having suicide rates almost three times the global average. Six of the top 10 countries by suicide rates globally are in the African region [2]. Meta-analyses have suggested that current rates of adolescent depression and anxiety are double pre-pandemic levels – worrying trends that may relate to even higher risks of suicidal behavior in this already at-risk group [3] These data have caused countries such as the US to deliver rare public health advisories about the urgent need to address youth mental health [4].

**Fig. 1 Fig1:**
[figure not shown]
Mozambique with focal province of Sofala outlined in red. Figure sourced from Fernandes QF et al. (2014)

Limited research exists on youth suicide in the African WHO region and few to no evidence-based preventative interventions have been tested in LMICs more generally. On October 6th, 2022 the WHO launched a global campaign highlighting the urgent need to raise awareness and galvanize action for suicide prevention in the African region calling it a “crisis in Africa” [5]. Recent systematic reviews have shown that, while global suicide rates have fallen over the past decades, rates of suicide in LMICs continue to be high – especially for youth and young adults [6] – and in many African countries suicide rates are increasing [7]. Despite the high burden of suicide, LMICs and specifically the African region, are extremely underrepresented in research. A recent systematic review evaluating the effect of the COVID-19 pandemic on suicidal behavior noted a complete absence of any research from the African continent [8]. Systematic reviews of suicide prevention interventions in LMICs have shown a paucity of existing research on best evidence approaches, such as safety planning and support for individuals after suicide attempts [7]. A 2022 systematic review of suicide prevention studies among youth in LMICs [9] found only one small pilot study conducted in the African WHO region (South Africa) testing a brief suicide intervention among individuals living with HIV.

Suicide and suicidal behaviors are an urgent public health problem in Mozambique, with rates highest among adolescents and young adults, yet prevention interventions are unavailable. In a seminal 2013 study, our team showed that over 16% of suicide deaths from legal medicine autopsies were adolescents under the age of 18 and 48% of deaths were young people under the age of 25 [10]. Another representative community household study of 3,080 individuals by our team in Sofala and Manica Provinces showed that of the 17% of the sample reporting lifetime suicidal ideation, only 3.8% ever received any treatment for their suicidal thoughts [11]. We recently completed a study of adult suicidal behavior in primary care in Sofala Province showing strong associations with younger ages and high rates of suicidal plans; over 85% of those aged 18–24 with suicidal ideation had made a suicide plan and 65% of those with a suicide plan made a suicide attempt. These data suggest the urgent need to intervene in the prevention of suicide attempts specifically for younger individuals in Mozambique as the cascade from ideation to planning to attempt is very high in this context [12]. Last, a pilot study by our team among adolescents 12–19 in grades 8–12 in Mozambique secondary schools found 16% reporting past month suicidal thoughts, 11% reporting suicide planning, and 6% with past-month suicidal behavior; lifetime suicide attempts were also high at 9% of adolescents [13]. Despite these alarming statistics, no youth suicide prevention approaches have been tested or implemented in Mozambican schools.

Suicide safety planning and cognitive behavioral interventions to reduce suicide are best evidence interventions to reduce suicidal behavior in high-income contexts yet have never been tested in the African WHO region. A 2021 meta-analysis [14] of the effectiveness of suicide safety planning interventions showed very large effects on suicidal behavior (RR: 0.57; 95% CI: 0.41–0.79). Another more recent meta-analysis of the Safety Planning Intervention (SPI) found 26 studies globally [15], with only a single quasi-experimental study in a LMIC (India). This study found SPI to be feasible, acceptable, and flexible to various contexts. Meta-analyses of cognitive behavioral interventions to reduce suicide have also consistently shown very strong effect sizes in the reduction of suicidal behavior [16–19]. Yet, few studies have been conducted with adolescents and to our knowledge none of these systematic reviews include a single study testing cognitive behavioral interventions to reduce suicide in the African continent. In high-income settings, extensive evidence has been developed regarding SPI and cognitive behavioral interventions for the prevention of suicidal behavior, and in many contexts both interventions are being or have been scaled-up. Since 2016, the United States Joint Commission has recommended SPI as standard of care for suicide prevention [20]. By contrast, no high-quality evidence exists for the effectiveness of either SPI or cognitive behavioral interventions for suicide prevention in LMICs. This lack of evidence is directly hindering the ability to scale-up best evidence interventions to address the urgent need for suicide prevention in areas with the highest suicide rates globally [21, 22].

The Common Elements Treatment Approach—Mozambique (CETA-MZ) CBT-based transdiagnostic therapy is feasible, acceptable, and associated with decreases in depressive symptoms and suicidal ideation in Mozambique. Starting in 2018, our team led the adaptation of CETA to the Mozambican context. This included training/supervision of non-specialist healthcare workers and a demonstration project to test feasibility, acceptability, and clinical outcomes among patients testing HIV + in primary care clinics of Sofala, Mozambique. Initial data suggested that, among youth 18–24, CETA-MZ was associated with an 80% reduction in depression symptoms and a reduction in suicidal ideation from 20% at intake to < 3% after 5 sessions [21]. CETA and other cognitive behavioral interventions have also been tested in other contexts showing feasibility, acceptability, and effectiveness among youth < 18 and in schools [22–26].

We believe that these two evidence-based practices, both with demonstrated feasibility in Mozambique, have the potential to be powerful interventions to prevent adolescent suicidal behavior. Yet, a recent meta-analysis found lower comorbidity of psychiatric disorders and suicidal behavior in LMICs (~ 50%) compared to high-income countries (~ 90%) [27]. Therefore, it is possible that applying CETA-MZ to address psychiatric symptoms may not lead to significant decreases in suicidal behavior above and beyond SPI alone. For these reasons, we propose to test both SPI alone and the integration of SPI into CETA-MZ – adapted for adolescent suicide prevention – to create a Transdiagnostic Cognitive Behavioral Therapy for Suicide (TCBT-S) delivered by non-specialists in Mozambican secondary schools. Due to limited resources for mental health in the African region we aim to test whether the potential gains in effectiveness with the more resource intensive TCBT-S justify its scale-up versus the brief SPI intervention alone. This study will be conducted using a three-arm parallel Hybrid Type-1 cluster randomized trial design across 21 schools (7 to each arm of Enhanced Usual Care [EUC], SPI alone, and TCBT-S). This study will also generate evidence on costs, implementation determinants, and potential mechanisms of intervention effects to optimize intervention components and implementation strategies for future scale-up, if effective.

## Methods

### Safety Planning Intervention (SPI) specification and processes

SPI is an evidence-based brief intervention (~ 30–45 min) that provides strategies to decrease the risk of suicidal behavior (Fig. 2). It has been shown to be effective at reducing suicidal behavior in adults and adolescents in high-income countries [28–30] and is a best practice for the Suicide Prevention Resource Center/American Foundation for Suicide Prevention [30]. SPI begins with psychoeducation about suicide risk followed by a collaborative approach to create a stepwise safety plan that includes a list of individually tailored, concrete coping mechanisms to be enacted during or leading up to a crisis. The six steps of the safety plan include: 1) recognizing warning signs of a crisis; 2) employing internal coping strategies; 3) using social contacts and settings to distract from suicidal thoughts; 4) seeking help from family members or close friends; 5) contacting healthcare or emergency services; and 6) reducing access to means [28, 31].

**Fig. 2 Fig2:**
[figure not shown]
Schematic of the components of the Safety Planning Intervention (SPI)

### Transdiagnostic CBT-based intervention for Youth Suicide Prevention (TCBT-S) specification and processes

CETA-MZ is an evidence-based, manualized transdiagnostic CBT-based protocol to address co-morbid common mental disorders [32]. CETA-MZ leverages the commonalities in CBT approaches to treatment of depression, anxiety, and PTSD in a single flexible intervention for one or more of these often-overlapping disorders. CETA-MZ is a Mozambique adaptation of CETA that has been adopted by the Ministry of Health for national scale-up in HIV/AIDS settings [21, 33]. The present study will optimize CETA-MZ clinical protocols to specifically address youth suicide prevention as well as integrate the full SPI intervention simultaneously to create a novel Transdiagnostic CBT-based Intervention for Youth Suicide (TCBT-S); (Fig. 3) [34]. We will retain individual modules: (1) Psychoeducation (CETA module “Introduction/Encouraging Participation”); (2) Behavioral Activation (“Getting Active”); (3) Cognitive Restructuring (“Thinking in a Different Way Part 1 & 2”); (4) Problem Solving (“Resolving Problems”); and (5) Distress Management and Relaxation Strategies (“Relaxation”). SPI will be embedded in TCBT-S, including creation of the safety plan at first contact, and revisiting the plan at following visits to make plan adjustments, if needed [34]. Adaptations to CETA-MZ modules will include: i. psychoeducation focused on suicidal thoughts and behaviors and how TCBT-S is expected to contribute to recovery; ii. cognitive restructuring adapted to focus on the thoughts and feelings that occur during, or leading up to, suicidal thoughts or behaviors and techniques for evaluating and reframing firmly held thoughts that can contribute to suicidal crisis; iii. linking behavioral activation to coping strategies included in the safety plan for acute distress tolerance and crisis avoidance; iv. problem solving focused on addressing problems believed to be contributing to suicidal thoughts and behaviors; and v. distress management and relaxation strategies specifically targeted towards emotional regulation to manage overwhelming physical and emotional response contributing to suicidal thoughts and behaviors.

**Fig. 3 Fig3:**
[figure not shown]
Schematic of the components of the Transdiagnostic CBT-based Intervention for Youth Suicide Prevention (TCBT-S)

### Study aims

In this proposal, we will conduct a Hybrid Type 1 effectiveness/implementation study, following the typology outlined by Curran et al. [35, 36]. In a Hybrid Type 1 study, the primary study aim is to test clinical intervention effectiveness paired with a secondary aim to better understand implementation outcomes and the implementation context. Type 1 trials are best in situations where an intervention has strong face validity and indirect evidence for applicability to the population in question which we argue hold given extensive evidence for effectiveness of SPI and CBT interventions for suicide prevention in high-income contexts. We use the SPIRIT guidelines to structure this study protocol [34].

The present project proposes to conduct a 2-year parallel Hybrid Type-1 cluster RCT, randomizing 21 government secondary schools to enhanced usual care (EUC), Safety Planning Intervention (SPI) alone, and the Transdiagnostic CBT-based Intervention for Youth Suicide (TCBT-S); (Table 1). Primary study outcomes will be evaluated at 6 months post intake, with maintenance indicators at 12 and 24 months. A sub-aim of the cluster RCT will be an exploratory evaluation of causal pathway models to examine mechanisms of action of SPI and TCBT-S interventions using longitudinal structural equation modeling.

Alongside testing intervention effectiveness, we will unpack implementation context and potential problems associated with real-world implementation by linking quantitative implementation outcomes based on the RE-AIM evaluation [37] with determinants (barriers/facilitators) based on the Consolidated Framework for Implementation Research (CFIR) [38, 39]. Last, we will estimate the incremental cost and cost-effectiveness of scaling-up SPI and TCBT-S in Mozambique using micro-costing, time-and-motion observation, and a Markov model parameterized with cost and outcome data from the SPI and TCBT-S cluster RCT.

**Table 1 Tab1:**
[figure not shown]
SPIRIT project activities and timeline

### Overview of study design

Following IRB approvals, planning meetings, and randomization of secondary schools, our team will recruit non-specialist healthcare workers and train them to lead screening activities using the Columbia Suicide Severity Rating Scale (C-SSRS) for youth [40, 41] as well as EUC, SPI, or TCBT-S treatment protocols (see Table 1 for full study timeline). The C-SSRS defines clear levels of suicide risk and guidance for their use in clinical trials that have been adopted by the FDA [42]. Youth enrolled in grade 10 at target schools (Table 2) will be screened for active suicidal ideation in the past month and those who screen positive (responding affirmatively to “have you actually had any thoughts about killing yourself?” on the C-SSRS) will be enrolled in EUC, SPI, or TCBT-S respectively until recruitment targets are met. EUC protocols will apply to all arms of the study and include identification of suicide risk through the C-SSRS. Those determined to be high risk using the C-SSRS will be transported to local government emergency mental health services that [name] (Co-I) directs in his role as Provincial Director of Mental Health services in Sofala Province. All selected schools have nearby emergency psychiatric and psychological services (< 30 min); (Table 2). These activities will include collaboration with Youth Friendly Services at each health facility. EUC activities will be implemented by nonspecialist healthcare workers who will participate in a 3-day practical training provided by Mozambican SPI/TCBT-S trainers supervised by Drs. [name], [name], and [name]. For students with moderate risk, they will receive information and referral to local government mental health and youth friendly services. At follow-up outcome ascertainment timepoints, those in the EUC arm will be re-assessed for suicide risk and uptake of referral services.

**Table 2 Tab2:** Target schools and characteristics

N	School	# Enrolled in 10th Grade, 2024	Referral Health Facility	District	Urban, Rural, or Peri-urban
1	Escola Secundária da Ponta Gea	542	CS Ponta Gêa	Beira	Urban
2	Escola Secundária Samora Moises Machel	1134	CS da Ponta Gêa	Beira	Urban
3	Escola Secundária Mateus Sansão Mutemba	1674	CS da Ponta	Beira	Urban
4	Escola Secundária da Manga	1433	CS de Nhaconjo	Beira	Urban
5	Escola Secundária do Estoril—Macuti	1051	CS de Macurungo	Beira	Urban
6	Escola Secundária 25 de Setembro—Chamba	594	CS de Inhamizua	Beira	Peri-urban
7	Escola Secundária de Marocanhe	864	CS Mascarenhas	Beira	Peri-urban
8	Escola Secundária de Matadouro	1131	CS de Inhamizua	Beira	Peri-urban
9	Escola Secundária de Muchatazina	860	CS da Munhava	Beira	Urban
10	Escola Secundária do Dondo	1105	CS de Dondo	Dondo	Urban
11	Escola Secundária de Mafambisse	926	CS de Mafambisse	Dondo	Rural
12	Escola Secundária de Macharote	840	CS de Dondo	Dondo	Peri-urban
13	Escola Secundária Graça Machel-Dondo	395	CS de Dondo	Dondo	Rural
14	Escola Secundária Filipe Samuel Magaia	305	CS de Mafambisse	Dondo	Rural
15	Escola Secundária de Nhamatanda	729	HR de Nhamatanda	Nhamatanda	Peri-urban
16	Escola Secundária de Lamego	244	HR de Nhamatanda	Nhamatanda	Rural
17	Escola Secundária de Metuchira	445	HR de Nhamatanda	Nhamatanda	Rural
18	Escola Secundária Marcelino Dos Santos	630	HR de Nhamatanda	Nhamatanda	Peri-urban
19	Escola Secundária Mathias Manuel Kaphesse	713	HD de Caia	Caia	Peri-urban
20	Escola Secundária de Inhaminga	542	CS de Inhaminga	Cheringoma	Rural
21	Escola Secundária de Muxúngue	275	HR de Muxúngue	Chibabava	Rural

In the SPI only arm, following previously tested and piloted protocols in Mozambique, non-specialist healthcare workers will participate in a 5-day practical training provided by Mozambican SPI trainers. Following the apprenticeship model [43], SPI providers will role-play suicide screening and SPI protocol implementation in weekly supervision meetings with trainers. Once providers show competence in role-play they will be certified using the Safety Plan Intervention Rating Scale for Mozambique (SPIRS-MZ) [44] where they will have to achieve adequate or better rating on each scale domain. Consistent with expert recommendations on SPI [28, 31], youth will receive follow-up contacts at two and four weeks post intake to assess risk and review their safety plan. Safety plans will also be reviewed during outcome measurements at 3, 6, 12, and 24 months.

### Study setting

Sofala Province (population ~ 2.4 million; Fig. 1) was selected because of the deep relationship between investigators and the local MoH as well as the absence of existing interventions for youth suicide prevention. While only approximately 40–50% of youth in Mozambique attend secondary school [45], the decision to implement the present study in secondary schools in Sofala, Mozambique was based on: (1) our previous challenges with longitudinal treatment of youth in primary care settings; (2) feasibility of recruiting a large cohort of youth with active suicidal ideation as well as treatment stigma in community settings; and (3) preliminary studies documenting high rates of suicidal behavior among secondary students. If effective, we see potential for SPI or TCBT-S to be scaled-out and implemented in other community-based healthcare settings, such as youth friendly health services, emergency rooms, or primary care settings for larger population reach. In Mozambique, over 98% of formal health services are offered through the Ministry of Health [46], improving the potential for rapid national scale-up when collaborating and implementing within the centralized government systems. This has been the case with the original CETA-MZ intervention, which is currently being scaled-up nationwide in HIV/AIDS care settings.

### Study outcomes

Primary study outcomes will be youth-level suicidal behavior in the past month (primary), suicidal ideation in the past month (secondary), depressive symptoms in the past 2 weeks (secondary); (Table 3). Suicidal behavior was selected as the primary trial outcome due to previous meta-analyses showing SPI and CBT interventions for suicide prevention to have the strongest effects on reducing suicidal behavior [14, 17]. In the present trial, all primary and secondary outcomes will be collected at 3-, 6-, 12-, and 24-months post intake. Primary analyses will occur at 6 months following the strongest evidence from previous trials. Secondary outcomes of suicidal ideation and depressive symptoms are included due to mixed evidence on these outcomes from CBT-based suicide prevention meta-analyses [16, 17]. The DSM-5 crosscutting assessment and the RCADS-25 youth will also be collected at all timepoints due to requirements imposed by the NIMH Common Data Elements [47]. As shown in Table 3, suicidal behavior will be measured through reported actual suicide attempts, interrupted attempts, aborted attempts, or specific preparatory acts or behavior reported on the C-SSRS for youth [40, 41]. Our team has previously translated, adapted, and applied the C-SSRS to evaluate suicidal behavior among youth in schools in Mozambique and the instrument was acceptable, appropriate, and feasible to implement [13]. Suicidal ideation will include active suicidal thoughts reported in the past month on the C-SSRS. Clinically-significant depressive symptoms will be measured through the PHQ-9-MZ, a Mozambique adaptation of the PHQ-9 that our team has previously validated for use in Sofala, Mozambique [48]. Patient-level data collection will be done in CommCare [49], which our team is currently using for longitudinal patient tracking for a mental health cRCT in Sofala Mozambique [47]. All data will be stored on encrypted and password protected computers, accessible only to the named study staff. Any identifying features needed to link follow-up of patients over time will be destroyed at the end of the 24-month follow-up period.

**Table 3 Tab3:** Primary and secondary clinical outcome indicators and definitions

Outcome	Indicator	Definition
PRIMARY	Suicidal behavior in past month	Actual suicide attempt, interrupted attempt, aborted attempt, or specific preparatory acts or behavior reported on the C-SSRS in past month
SECONDARY	Suicidal ideation in past month	Non-specific active suicidal thoughts reported on C-SSRS in past month
SECONDARY	Depressive symptoms in past two weeks	PHQ-9-MZ score ≥ 10 referring to symptoms in the past 2 weeks

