### Primary statistical analyses

Individual-level primary and secondary outcome data will be analyzed using generalized linear mixed models using the binomial family, logit link, and random effects at the school and individual level. Primary analyses will compute odds ratios for suicidal behavior in the past month comparing the SPI alone and the TCBT-S arms to EUC; primary outcome analyses will be done at 6 months post intake. We will also conduct supplementary analyses of primary and secondary outcomes at 3 months post intake. Sensitivity analyses will utilize gaussian models to directly compute differences in the proportion of SPI and TCBT-S with suicidal behavior compared to EUC. Student (age, sex, grade) and school (size, location) will be considered for inclusion based on balance. Secondary analyses will utilize the same modeling approaches to evaluate odds ratios for suicidal ideation and PHQ-9 ≥ 10 as well as directly comparing outcomes between SPI alone and TCBT-S arms. We will also examine absolute differences in PHQ-9-MZ scores across groups using gaussian models. Sex as a biological variable will be assessed using pre-specified interaction sub-analyses to examine differential SPI and TCBT-S effects for females vs. males. For the RE-AIM maintenance domain, we will repeat all analyses at 12 and 24 months. All statistical analyses will be conducted blinded to study arm.

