### SPI/TCBT-S mechanisms assessment approach

Building on existing published theoretical models of SPI and TCBT-S [30, 59], ongoing studies examining mechanisms of effects [60–62], as well as recent reviews [63] proposing mechanisms of action for SPI and cognitive behavioral interventions for suicide prevention [64] we have specified an intervention-mechanism-outcome conceptual model including six hypothesized mechanisms of action for effects of SPI alone and TCBT-S (see Fig. 5). Utilizing mechanism outcome data collected at intake and longitudinally we will test effects of hypothesized mechanisms and moderators using longitudinal structural equation modeling. Hypothesized mechanisms, preconditions, and moderators will be collected at intake and each effectiveness outcome measurement (3, 6, 12, and 24 months). Table 6 summarizes use of validated measurement approaches [65–70] (where available) to be used for each mechanism. To facilitate feasibility of measurement across numerous mechanisms scales, our team adapted questions from otherwise validated measures (Table 6), selecting questions with high factor loadings from applicable constructs. Primary analyses of mechanisms will occur at the end of the primary effectiveness outcome (6 months). Secondary analyses will occur at the end of the maintenance phase (24 months).

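### The stated covariate list omits the intake PHQ-9-MZ score, although it is collected and would sharpen both planned depression analyses at no cost

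*Protocol article*

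**What the plan says.** Study outcomes, Table 3, defines the secondary depression outcome as "PHQ-9-MZ score ≥ 10 referring to symptoms in the past 2 weeks". Primary statistical analyses gives its model: "Secondary analyses will utilize the same modeling approaches to evaluate odds ratios for suicidal ideation and PHQ-9 ≥ 10". The same section then adds the score itself: "We will also examine absolute differences in PHQ-9-MZ scores across groups using gaussian models".

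On covariates that section says: "Student (age, sex, grade) and school (size, location) will be considered for inclusion based on balance". The mixed models carry "random effects at the school and individual level".

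Study outcomes schedules the primary and secondary outcomes at 3, 6, 12 and 24 months after intake. That the PHQ-9-MZ is also taken at intake follows from two other places. Table 6 lists depressive symptoms, measured by PHQ-9-MZ, as a moderator, and the mechanisms section says: "Hypothesized mechanisms, preconditions, and moderators will be collected at intake and each effectiveness outcome measurement".

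Entry is on active suicidal ideation in the past month (Overview of study design), with no depression threshold. Randomisation is constrained on school size and location only (Sampling and randomization procedures).

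**The concern.** Entry does not restrict the PHQ-9-MZ, so intake scores may vary widely among enrolled youth. Much of the variation at 6 months is then likely to be carried over from intake, and a model without the intake score treats it as noise. The protocol does more than stay silent on adjustment. It names a covariate list, leaves out the measure most directly related to this outcome, and makes inclusion depend on observed balance. Balance is a poor criterion here, because a strong baseline predictor improves precision even when the arms are balanced on it.

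Intake depression is also not a constraint in the randomisation. With 7 schools per arm, a chance imbalance is possible, and the listed covariates would not directly correct it.

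Study outcomes includes depressive symptoms because earlier evidence is mixed. The plan also compares SPI directly with TCBT-S, where a depression difference could be smaller than against EUC. An imprecise depression result would be harder to interpret in either comparison.

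**Working it through.** **The plan's own figures.** The only stated power is for suicidal behavior (Table 4). With 100 youth per school and ICC 0.02, the design effect is 1 + 99 × 0.02 = 2.98 and the effective n per arm is 700 / 2.98 = 234.9. A two-proportion normal approximation at two-sided 0.025 from 37% gives 0.76, 0.91 and 0.98 for decreases of 12.5, 15 and 17.5 points. Table 4 has .76, .92 and .98. All 20 cells reproduce within 2 points. No power is stated for depression.

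**Inputs for depression.** From the protocol: 7 schools per arm and 100 youth per school. Assumed: SD 5 points; ICC 0.02 on the score (the protocol gives 0.02 for its power calculation on suicidal behavior); intake/follow-up correlation r of 0.4 to 0.6; 30-70% of EUC at or above 10; two-sided 0.05 for a secondary outcome; no dropout; normal approximation.

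**Plain score.** Between-school variance = 0.02 × 25 = 0.5 and within-school variance = 24.5. Variance of the arm difference = 2 × (0.5 + 24.5/100)/7 = 0.2129, so SE = 0.461. Power for 1.0 point = Φ(1/0.461 − 1.96) = 0.58.

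**Intake-adjusted score.**
- Gain within schools only: variance = 2 × (0.5 + 0.245 × (1 − r²))/7. This is 0.2017 for r = 0.4 and 0.1877 for r = 0.6, so SE is 0.449 and 0.433 and power is 0.61 and 0.64.
- Gain at both levels: variance = 0.2129 × (1 − r²). This is 0.1788 and 0.1362, so SE is 0.423 and 0.369 and power is 0.66 and 0.77.

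**Cut at 10.** The score is treated as normal and cut so that a proportion p of EUC is at or above 10. ICC on the binary scale = 0.02 × density² / (p(1 − p)), and design effect = 1 + 99 × ICC. For p = 0.5: ICC = 0.02 × 0.399² / 0.25 = 0.0127, design effect 2.26, effective n 309.7. A 1.0-point shift (0.2 SD) moves 50% to 42.1%, SE is 0.0399 and power is 0.51. Across p from 0.3 to 0.7, power is 0.48 to 0.51.

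| True difference | Cut at 10 | Plain score | Adjusted, within-school gain only | Adjusted, gain at both levels |
|---|---|---|---|---|
| 1.0 point | 0.48-0.51 | 0.58 | 0.61-0.64 | 0.66-0.77 |
| 1.5 points | 0.80-0.85 | 0.90 | 0.92-0.93 | 0.94-0.98 |

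**Cross-check by simulation.** The settings were 7 schools of 100 per arm, a 0.25 SD shift, 30-50% of controls above the cut, r of 0.3 to 0.7, a school-level intake/follow-up correlation of 0.5, and 4,000 runs per setting. Power was 0.65-0.71 for the cut, 0.70-0.82 for the cut with intake, 0.77-0.78 for the score and 0.84-0.90 for the score with intake. Intake adjustment added 5 to 12 points of power to the cut and 6 to 13 to the score. If intake removes only within-school variance, the adjusted score gives 0.79, 0.81 and 0.84 for r = 0.3, 0.5 and 0.7.

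**The case against.** The strongest reply is that the plan already analyses the score. That stands. Most of what dichotomising loses is recovered by the planned Gaussian model, and a reader who infers that the continuous information is thrown away would be wrong. What intake adjustment adds to the score is smaller: 0.03 to 0.06 in power for 1.0 point if only within-school variance is explained.

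A second reply is that the article does not say the analyses are unadjusted for intake, and that baseline handling is often left to a statistical analysis plan. The individual-level random effect could also point to a repeated-measures model that takes in the intake value. This stands in part, because non-use of the intake score is inferred and not declared. But the article does state a covariate list and a rule for choosing from it, and the intake score is outside that list.

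A reader might also infer that many youth start below 10 and so cannot show improvement. The documents do not support this. No intake PHQ-9-MZ distribution is given. The roughly 50% comorbidity figure in the Background concerns psychiatric disorders with suicidal behavior across LMICs, not PHQ-9-MZ scores in pupils with ideation. Nor does starting below 10 make a participant uninformative: such youth can cross upwards, and new onset counts in a comparison between randomised arms.

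Finally, the threshold serves a purpose. It expresses clinically significant symptoms and gives an odds ratio on the same scale as the other outcomes. Whether the score or the threshold should lead is closer to a preference than an error.

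**Conclusion.** The point holds as an optional improvement to a stated method. The listed covariates omit a baseline value that the trial will collect and that probably predicts the depression outcome well. Under the assumptions above, adjusting the score for intake raises power for a 1.0-point difference from 0.58 to between 0.61 and 0.77. Where it falls in that range depends on the correlation and on whether intake also explains differences between schools. The threshold analysis gains as well, by 5 to 12 points in the simulated settings.

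The size rests on an SD, score ICC, correlation and EUC prevalence that the documents do not give. The order of the analyses (cut, plain score, adjusted score) was the same in every setting tried. The planned threshold comparison is valid, and depression is a secondary outcome with no power target.

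**What to change.** In Primary statistical analyses, state that the intake PHQ-9-MZ score enters both the ≥ 10 model and the Gaussian score model as a fixed covariate, regardless of observed balance. If a repeated-measures model is intended, say how the intake value enters it. Report the intake-adjusted 6-month score difference together with the ≥ 10 odds ratio as a co-reported depression result. Showing the ≥ 10 result separately for youth below 10 and at or above 10 at intake is optional.

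The cost is a sentence or two of text and no new data. Two consequences should be accepted in advance. The odds ratio becomes conditional on the intake score, so it is not numerically comparable with an unadjusted one. And with two depression results side by side, the text should say beforehand how they will be read if they differ.
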